**Explanatory Note:**

This is a common protocol for three drug trials. Each drug trial is an independent controlled two arm study to evaluate a selected Ayurvedic formulation (AYUSH 64 or Yashtimadhu or Samshamani Vati Plus) as described in this protocol.

The protocol is registered with Clinical Trials Registy India (CTRI).(<https://ctri.nic.in/Clinicaltrials/login.php> ).

# DISCLAIMER

The protocol is based on standard medical and scientific knowledge and experience, and personal opinion of the authors. Scientific deliberations and discussions and comprehensive reference to suitable published medical literature were used to arrive at consensus and prepare this protocol. This is a research protocol and not a document to guide any kind of health or medical practice and all study personnel and patients in the study/drug trials are strictly advised not to use any kind of medication based on this protocol without the explicit knowledge and permission of a qualified physician. The authors claim no responsibility for any act of omission or commission that may arise from this protocol and adversely impact the study or its participants in any manner.

The draft protocol versions went through several cycles of peer review by representatives of Indian Council of Medical Research and independent reviewers. The protocol version 3.3-F is finalized after considering the comments and suggestions from the reviewers. Names and affiliations of reviewers are provided in Appendix U.

# PRINCIPAL EXECUTIVE STATEMENT ON SPONSORSHIP AND FUNDING

This study is part of inter-ministry collaborative initiative of Government of India (GOI) involving Ministry of Health and Family Welfare (MoHFW), Ministry of AYUSH (MoA), Ministry of Science and Technology (MS&T) through Council for Scientific and Industrial Research (CSIR) with technical support and guidance from Indian Council of Medical Research (ICMR). This collaborative study is sponsored and funded by Ministry MoA and CSIR.

A common mechanism (under progress) worked out under the collaborative effort of AYUSH and CSIR (GOI) will ensure that all the required obligations and permissions and all statute requirements of the current study are satisfactorily complied with by the various stakeholders. The latter mechanism will also look after all matters pertaining to funding of the study and speedy dispersal of study funds and payments to the study personnel, supervision and monitoring of study, co-ordination between different stakeholders for smooth and speedy conduct and completion of study, speedy and suitable procurement of all study materials, obtaining all ethics and other mandatory clearances from appropriate regulatory bodies for the study and any other administrative matter that may impact the study adversely. All patients and investigators and study personnel will be protected against any unintentional and inadvertent liability including any kind of financial or legal prosecution arising from any aspect of this protocol or subsequent conduct of the study in any form by the AYUSH and ICMR GOI. It is prudent to add that any allegation of ‘personal negligence’ arising out of this protocol or its subsequent conduct in any form will be thoroughly scrutinized and investigated by the appropriate authority and may call for further legal action and possible prosecution.

**Note:**

- Each study site shall have at least two Principal Investigators, one each from Ayurevda and modern medicine.
- Additional study sites and PIs may be added based on clearances from respective IECs

# STUDY SYNOPSIS

**a. Background:**

Coronavirus Disease-19 (COVID-19) pandemic has unleashed an unprecedented damage to life and livelihood. Over four Million people have contracted the disease globally and almost 2.7 lakh have died by the end of April 2020. There is no specific therapy and the vaccine is likely to be ready by early 2021 if not earlier. All the global strategies are focussed on stringent measures to contain the virus and mitigate the suffering of the people. India is under lockdown since early March 2020 and the situation though grim is fairly stable. There is an upward trend in number of cases but the health care system is suitably meeting the challenge. Clinical research is a vital part of such epidemics. There is a dire need to find newer more effective drugs or at least improve the current standard of care.

India has a rich tradition of Ayurveda since ancient times and several ‘Rasayana’ drugs are well known to enhance the immunity status. Though COVID 19 is an acute infectious disease with a predominant affliction for lungs and airways, the clinical experience so far has shown a rapidly progressive inflammation triggered by several exuberant immunological events. Therefore, there may be a potent role of immunity enhancing and or immunomodulators drugs in the medical management of COVID 19. It is against this perspective that the Ministry of AYUSH and Council of Scientific & Industrial Research (CSIR) have initiated an ambitious and comprehensive research program to discover Ayurveda formulations with proven value in the chemoprophylaxis and treatment of COVID 19.

In this protocol, the focus is on medical treatment.

Three Ayurveda herbal formulations are selected – AYUSH-64 (a proprietary multi plant formulation of CCRAS), Yashtimadhu (*Glycyrrhiza glabra extract* extensively researched by IIIM, Jammu) and ‘Samshamani Vati Plus’ a classical formulation (*Tinospora cordifolia* plus *Piper longum*).

This protocol is common to study all the three formulations; however, any one of them at a time will be individually evaluated for efficacy in a separate randomized two-arm controlled study.

**b. Study title:**

A Randomized, Open Label, Parallel Efficacy, Active Control, Multi-Centre Exploratory Drug Trial to Evaluate Efficacy and Safety of an Ayurvedic Formulation as Adjunct Treatment to Standard of Care for the Management of Mild to Moderate COVID-19 Patients.

**c. Objective:**

**Primary:** To compare the efficacy and safety of a combination regimen of standard of care (SOC) plus a selected standardized Ayurvedic drug (as adjuvant) in the management of mild to moderate cases of COVID-19 with that of standalone SOC control (active control).

**Secondary:** The secondary objectives are (i) To determine the effect of combined standard of care plus Ayurveda drug on the surrogate markers of disease severity and progression, and recovery (ii) To identify predictors of drug response (iii) To describe the clinical phenotype (with reference to characteristics, timelines of occurrence of complications and course of illness)

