**n. Statistical statement:**

The design of the drug trial is exploratory in nature. Though a randomized selection of patients will be done to either of the two arms, the sample size is that of convenience (expert opinion) and the same is not statistically powered however, sample size (70 patients in each arm) sufficient to draw meaningful conclusions. The statistical significance p<0.05(two sided) is predefined for analysis. Statistical analysis will be performed using standard tests to compare the two interventional arms for primary and secondary efficacy measures. Safety events will be also analyzed. Both intent-to-treat and per protocol completer analysis will be performed. Regression analysis will be done to identify predictors of response.

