**SECONDARY**

1. To determine the therapeutic effect of a combination of SOC plus a selected standardized Ayurvedic drug on surrogate markers of COVID-19 disease severity and complications, and recovery pertaining to broad based domain of acute phase reactants, pro-inflammatory cytokines, imaging assessment, anti-oxidant activity, organ dysfunction and damage
2. To determine the early and late post-recovery health benefits of a combination of selected standardized Ayurvedic drug plus SOC using qualitative measure of health status (WHO Quality of life assessment questionnaire) and health related behaviour, habits and fitness questionnaire
3. To describe the clinical profile of COVID-19 with special reference to early symptoms, severity of disease, complications, course of disease, diagnostic investigations, biochemical and imaging abnormalities, patterns of recovery
4. To determine the predictors of early and late recovery from COVID-19 using a therapeutic combination of SOC plus a selected standardized Ayurvedic drug

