**17.1 Sample Size:**

A convenience sample size of 70 patients in each of the arm is selected. The total sample size will be 140 patients in each of the 3 studies. The sample size is not based on any power calculations but by consensus within the experts of the Working Group constituted for the purpose of this protocol. It is assumed that the withdrawal rate may be in the range of 15-20%.

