**17.2 Statistical Analysis:**

Whenever suitable, both completer and an intent-to-treat analysis with ‘last observation carried forward’ will be performed; for intent-to-treat analysis the patient should have completed at least 4 weeks of intervention and completed the follow up visit at 4 weeks post enrollment.

All statistical processing will be performed using SPSS & BMDP software unless otherwise stated.

The data will be individually analyzed for central tendencies (mean, median), range, standard error, standard deviation and 95% confidence intervals for each intervention arm in each of the groups in the study. Data will be tabulated and graphically shown using standard format and MS Excel and other software programs. Though ANOVA will be used for most of the measures, standard parametric (Student t-test) and non-parametric statistical tests (Mann Whitney statistic, Kruskal Wallis test) will be used depending upon the normality of the data. Fisher’s exact test or Chi Square will be used to test the proportion of patients classified as efficacy failures and those with AE (calculate exact binomial 95% Confidence Interval).

The primary efficacy measures of ‘mean time to clinical recovery’ and ‘proportion of patients with clinical recovery’ in the two arms will be compared using appropriate statistical tests; ANOVA for ‘mean time’ and two proportion z-test for proportion of patients.

Secondary efficacy measures in the two arms will also be compared and Bonferroni correction will be applied for multiple comparisons.

Risk ascertainment will be done for selected variables. Regression analysis (multivariate and step down) will be used to identify predictors for important outcomes. Survival analysis will be carried out to compare the two interventions (HCQ and Ashwagandha) for primary efficacy at different study time points.

Within arm efficacy will be evaluated by a one sample Student t-test.

Significance for each statistical test result will be considered at two-sided p< 0.05.

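### The synopsis promises predictors of drug response, but the regression described relates patient features to outcome, with no stated treatment-by-feature comparison against standard of care

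*Combined protocol and SAP*

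**What the plan says.** The target is described in two ways.

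- Synopsis, c. Objective, secondary (ii): "To identify predictors of drug response". Synopsis, n. Statistical statement, carries this into the analysis: "Regression analysis will be done to identify predictors of response".
- Section 4, secondary item 4: "To determine the predictors of early and late recovery from COVID-19 using a therapeutic combination of SOC plus a selected standardized Ayurvedic drug". Section 17.2: "Regression analysis (multivariate and step down) will be used to identify predictors for important outcomes".

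The synopsis speaks of response, and in the objective of drug response. The body speaks of recovery and outcomes. Section 17.2 adds "Significance for each statistical test result will be considered at two-sided p< 0.05". It does not list candidate features, name the outcome scale, give the model terms or say whether one arm or both enter the model. No section mentions effect modification, treatment effects within subgroups or a treatment-by-feature term. The only interactions mentioned are pharmacological ones, in Appendix D.

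On size, Section 17.1 says "A convenience sample size of 70 patients in each of the arm is selected", "The sample size is not based on any power calculations", and "It is assumed that the withdrawal rate may be in the range of 15-20" per cent.

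**The concern.** Whether a feature predicts recovery and whether it predicts response to the drug are different questions with different null hypotheses. For the first, the null is that the feature is unrelated to outcome. For the second, it is that the drug-versus-SOC difference is the same at every level of the feature. A feature can be strongly prognostic and have no bearing on the drug's effect.

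The protocol itself names likely prognostic features. Section 2.1 describes the disease as more severe in the elderly and links severe and fatal cases to hypertension, cardiac disorders, diabetes and obesity. If such features emerge from the regression and are reported under the synopsis objective, readers will take them as guidance on who benefits from the tablets. The same text governs three separate drug trials, so the mislabelling could occur three times. The randomized SOC arm that could separate the two questions is already in the design.

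**Working it through.** **Starting point.** The plan has no power figure to reproduce. The only arithmetic it offers is 70 + 70 = 140 per trial, which agrees.

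**Inputs from the plan.** 70 per arm; two-sided alpha 0.05; withdrawal 15-20%, so at the upper end 70 × 0.80 = 56 per arm.

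**Assumptions (the plan gives none).** The drug has no effect. One feature has correlation r with a continuous outcome such as log recovery time, the same in both arms. Values r = 0.2, 0.3 and 0.4 are tried. Under this truth the feature does not predict drug response, so every significant result is a false label.

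**Step 1: analytic check.** The chance of a significant association is approximately Φ(atanh(r) × √k − 1.960). Here k = n − 3 for the drug arm alone and N − 4 for both arms with arm as a covariate.

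- Drug arm, n = 70, √67 = 8.185. r = 0.2: 0.2027 × 8.185 = 1.659, Φ(−0.301) = 38%. r = 0.3: 0.3095 × 8.185 = 2.534, Φ(0.574) = 72%. r = 0.4: 0.4236 × 8.185 = 3.468, Φ(1.508) = 93%.
- Both arms pooled, N = 140, √136 = 11.662. r = 0.2: Φ(0.404) = 66%. r = 0.3: Φ(1.650) = 95%. r = 0.4: Φ(2.981) = 99.9%.

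**Step 2: simulation of the same setting (3,000 trials each).**

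| Per arm | r | Drug arm only | Pooled, arm as main effect | Interaction test |
|---|---|---|---|---|
| 70 | 0.2 | 39% | 67% | 6% |
| 70 | 0.3 | 72% | 95% | 6% |
| 70 | 0.4 | 94% | 99.9% | 5% |
| 56 | 0.2 | 32% | 57% | 5% |
| 56 | 0.3 | 61% | 90% | 5% |
| 56 | 0.4 | 86% | 99% | 6% |

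The two steps agree within simulation error.

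**Step 3: a yes/no feature present in half the patients**, shifting the outcome by 0.3, 0.5 or 0.8 SD in both arms, 70 per arm. Drug arm only: 23%, 53%, 92%. Pooled with arm: 41%, 82%, 99.7%. Interaction test: 4.8%, 5.6%, 5.2%. The pattern does not depend on the type of feature.

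**Step 4: what an interaction test could detect.** For a half-and-half feature, the smallest interaction detectable with 80% power is 2 × (1.960 + 0.842) × √(2/n) in SD units.

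- n = 70: 2 × 2.802 × 0.1690 = 0.95 SD.
- n = 56: 2 × 2.802 × 0.1890 = 1.06 SD.

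To convert to days, take the recovery entry of 10 (7-14) days in literature Table 2 of Section 2. Assuming rough normality, SD ≈ (14 − 7)/1.349 = 5.2 days. The detectable interactions are then about 4.9 and 5.5 days. For an interaction only as large as the detectable main effect, power is Φ(2.802/2 − 1.960) = Φ(−0.559) = 29%.

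**The case against.** The best defence is that the model is unspecified rather than wrong. Sections n and 17.2 give one sentence each; an interaction term is absent, not ruled out. The body is also fairly consistent with itself: Section 4 item 4 and Section 17.2 both concern outcome, response is nowhere defined as a contrast with SOC, and no null hypothesis is stated. The objective is secondary in a trial labelled exploratory, and the primary comparison is untouched.

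Most of this stands, and it makes rewording the synopsis a legitimate remedy. It does not remove the problem. Neither available reading of the text, drug arm only or both arms pooled, answers the synopsis objective. Exploratory status excuses low power, not a test of a different question. The synopsis also says the sample suffices for meaningful conclusions.

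A reader might infer more than the documents support:

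- That any prognostic factor will be mislabelled. Weak ones often will not: at r = 0.2 with 56 per arm, a drug-arm fit flags 32%.
- That nearly all response will be natural recovery in either arm. Section 8 expects a large majority to recover completely, but does not speak of arms or of natural recovery.
- That a true modifier would be missed. If the feature has slope 0.5 under SOC and none under the drug, a drug-arm fit finds it in 5% of trials, but a pooled fit flags it in 90%, without being able to identify it as a modifier. The plan does not say which fit is meant. The interaction test's power here is about 82-91%, depending on the assumed residual SD.

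**Conclusion.** The concern holds in this form: the synopsis promises predictors of drug response, and the analysis described contains no stated comparison that could identify them. Followed as written, a sufficiently strong prognostic factor would be reported as a predictor of response to an inert drug. The illustrative frequency at 70 per arm is 39-94% (drug arm only) or 67-99.9% (pooled), against about 5% with an interaction test.

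These percentages are the power of an association test at assumed correlations, for one feature and complete data. They are not an error rate for the step-down procedure, which is too loosely specified to simulate. The qualitative conclusion does not depend on the exact values. The consequence is a misleading secondary claim, which is worth correcting before analysis.

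**What to change.** Choose one of two routes and make the synopsis, Section 4 and Section 17.2 agree.

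(a) Keep the drug-response objective. In Section 17.2, fit a model with both arms and a treatment-by-feature interaction for each of a short pre-listed set of baseline features already collected, for example age, days since symptom onset, mild versus pneumonia, comorbidity and baseline CRP. Report the treatment effect with its confidence interval at each level of the feature, and label the results exploratory. Call any feature without interaction evidence a prognostic factor for recovery.

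(b) Drop the claim. Reword synopsis objective (ii) and the synopsis statistical statement to prognostic factors for recovery, in line with Section 4 item 4 and Section 17.2. Draw no conclusion about drug response from that regression.

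Neither route needs new data, visits or patients. The cost of (a) is low power: only interactions of about 0.95 SD or more are detectable with 80% power at 70 per arm, so most results will be inconclusive. The cost of (b) is that the trial no longer claims to say who responds to the drug.

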**d. The investigational products:**

Three formulations will be used in the study; those will be separately used as adjunct treatment. These formulations are –Samshamani Vati Plus, AYUSH 64 and Yashtimadhu.

**e. Study duration:**

The total duration of the study is 12 weeks – this includes a period of hospital based treatment followed by a post recovery period. The Ayurvedic drug will be prescribed as per protocol for a total duration of 12 weeks.

**f. Study design:**

This is a prospective, randomized, open label, blinded end point (PROBE), parallel efficacy, multicentric, two arm study to compare the efficacy of a combination of Standard of Care (SOC) plus a selected individual Ayurveda herbal drug (Samshamani Vati Plus or AYUSH 64 or Yashtimadhu) to SOC (active control). The Ayurveda drug is being considered as an adjunctive or an add-on therapy and each of the three drugs will be evaluated in separate two arm trial with a common study design. The drug trials are ‘exploratory’ in design. The Study Flow diagram summarizes the study design and schedule of events (Fig 1) (Appendix A).

**g. Sample size:** The total sample size is 140 patients per drug trial- 70 patients in each arm.

**h. Study Population:** All adult patients with laboratory-confirmed SARS-CoV2 infection with mild to moderate category will be selected from the outpatient or inpatient facility in COVID-19 medical centers/hospitals. Voluntary patients will be explained about the study and if willing will sign the informed consent and be screened for eligibility.

**Fig 1: Study Flow Diagram with Schedule of Important Study Events**

Screening of Voluntary and Consenting In-patients suffering from Mild to Moderately Severe COVID-19 for Eligibility as per Inclusion-Exclusion Criteria

3 Ayurveda formulation drug trial studies under a common protocol

(Separate study for each AYUSH 64 / Yashtimadhu / Samshamai Vati Plus)

Randomize Eligible Hospitalized Patients

(Open Label, Parallel Efficacy, Active Control Standard of Care (SOC), Two Arm Study)

Selected Ayurveda Formulation (Adjuvant) Versus SOC (Active Control)

Time Points

Clinical Assessment

Investigations

Baseline

Case Record Form (CRF), Medical History Clinical Examination, Ayurveda Assessment, Health Status (WHOQs), QoL (HR-BHF)

Diagnostic (PCR), Serology (IgM, IgG), Routine Hematology Profile, Special Assays, X-Ray Chest & Imaging, ECG

Week 4

Brief Clin Exam, Ayu Exam, Health Status (WHO- Qs) & QoL (HR-BHF Qs), Adverse Events (AEs)

Diagnostic (PCR), Serology (IgM, IgG), Routine haematology Body Profile, Special Assays

Week 8

Brief Clin Exam, Ayu Exam, Health Status (WHO- Qs) & QoL (HR-BHF Qs), Adverse Events (AEs)

Diagnostic (PCR), Serology (IgM, IgG), Routine haematology Body Profile, Special Assays

Week 12

Completion Outcome Assessment, CRF Clin Exam, Ayu Exam, WHO- Qs & QoL (HR-BHF Qs), AEs

Diagnostic (PCR), Serology (IgM, IgG), Routine haematology Body Profile, Special Assays

***Further Assessment Time Points**: (i) During Hospitalization: Daily monitored vital parameters, disease symptoms, disease progression and recovery, and investigations carried out as per protocol till DISCHARGE; Laboratory and Imaging investigations as per protocol but the study investigator and treating physician can do any additional test as per their judgment (ii)Post DISCHARGE: Daily Telephonic Contact using a special mobile phone application for any relapse or any other symptoms or complications or any other Issue (iii) Discharge: Complete all formalities as required for study completion (iv) Skip week 4 or week 8 end point evaluation within 2 weeks of DISCHARGE

The total study period is 12 weeks; Primary Efficacy is ‘Clinical Recovery’ as described in the protocol; Study participant developing severe COVID 19 or severe complication and requiring special critical support/ ICU/ ventilator support will be withdrawn from the study but followed up to record outcome;

Both Ayurvedic and Allopathic Physicians will jointly examine and monitor study participants in addition to the hospital treating physician

**i. Eligibility:**

1. **Inclusion Criteria:**
2. Typical clinical presentation of acute onset febrile illness with cough and a RT_PCR based laboratory confirmation test for COVID-19
3. Patients with either sex, 18 to 75 years age
4. Patients with mild to moderate patients
5. All patients must agree not to share medication
6. Patients willing to participate and sign an informed consent
7. Exclusion Criteria:
8. Patients suffering from severe COVID-19 Disease as judged by a physician and fulfilling at least two of the following three criteria* (i) Respiratory distress at room ambience (≥30 breaths per min) (ii) Oxygen saturation at rest ≤93% (peripheral digital arterial oxymetry) and requiring oxygen support for over one hour to normalize (iii) Any of the known COVID-19 complications and emergency procedures which may require shift/admission in intensive care unit such as respiratory failure, adult respiratory distress syndrome, requirement of oxygen support for over 1 hour, requirement of mechanical ventilation, septic shock, or severe non-respiratory organ dysfunction or failure.
   (Adapted and modified from the reference: Yang Liu et al. Lancet Infect Dis 2020, 2020 https://doi.org/10.1016/ S1473-3099(20)30232-2)
9. Chronic, Severe, Unstable, Uncontrolled co-existent medical illness such as Diabetes, Hypertension, Cardiac disorders, liver, kidney disorders and lung disorders or other disease of concern which may put the patient at increased risk during the study
10. History of immunosuppression: solid organ or bone marrow transplant, use of immunosuppressive antimetabolic and biologic agents, intrinsic immunodeficiencies, HIV infection.
11. Active cancer diagnosis, on palliative treatment or requiring current therapy with antimetabolic agents, immunotherapy or radiotherapy.
12. Patients on parenteral nutrition
13. Patients with known sensitivity or contraindication to any of the ingredients of study medication
14. History of bleeding haemorrhoids, haemoptysis, acid peptic diseases, ulcers and pulmonary diseases (tuberculosis, asthma, etc.)
15. Patients who are likely to worsen or planed ICU admission or ventilator support due to any reason
16. Pregnancy and lactation
17. Participation in a drug interventional clinical drug trial of any nature in the three month period preceding onset of COVID-19
18. Participation in any other clinical trial of an experimental agent treatment for COVID-19
19. Patients on any kind of Ayurveda treatment or any other alternative and complementary medicinal systems such as Homeopathy, Unani, Siddha and in particular requiring oral therapy of any kind.
20. Physician decision that involvement in the study is not in the patient´s best interest

